## Abstract

**Background:**

There is evidence of an association between pulmonary function and various nutrients, although no association has been observed in our setting between the Mediterranean Diet (MD) eating pattern and improved lung function. The objective of this study is to evaluate the effect of an intervention designed to increase MD adherence on lung function in smokers with no previous respiratory disease.

**Methods/design:**

Randomized, controlled, parallel clinical trial. Setting: primary health care centers in Catalonia (Spain). Participants: Current smokers (cumulative > 10 pack-years) aged 35–70 years, with Internet access, who provide signed informed consent to participate. Intervention: A nutritionist will conduct a 2-year multicomponent intervention to increase MD adherence, based on: 1) a personalized dietary-nutritional education intervention, 2) a Web 2.0 approach, the DIET Blog of nutritional information, and 3) group sessions to increase motivation to increase MD adherence and motivation to make changes in eating habits. Annually, an office visit and one group session will reinforce the nutritional intervention. The control group will follow their usual diet, with general nutritional counselling. In both groups, a 14-item questionnaire will evaluate individual MD dietary patterns and forced spirometry will assess lung function. Analysis: Intention to treat. The unit of analysis will be the individual smoker. Primary outcome is lung function indicated by spirometry, FVC, FEV1 and FEV1/FVC %. Lung function parameters in both groups will be compared by adherence to the MD pattern.

**Discussion:**

The DIET study could contribute data on a protective action of the MD pattern on lung function in smokers. If so, this population may benefit from a nutritional intervention, along with the fundamental recommendation to stop smoking.

**Trial registration:**

ClinicalTrials.gov: NCT02151669. Registered 26 May 2014.

## Background

Diseases of the respiratory system are a public health problem of the highest order [1]. Although smoking is the major risk factor for respiratory disease, other factors such as environmental agents, respiratory infections, genetic disorders and eating habits may also affect lung function [2].

In our setting, smoking is the main cause in the etiopathogenesis of respiratory disease [3]. Inhalation of the particles found in tobacco smoke accelerates the age-related physiological decline of pulmonary capacity [4]. It has been estimated that each cigarette smoked exposes the smoker to 10^15^ free-radical particles, a major source of oxidative stress and inflammation [5]. To counteract this effect, the first line of defence is that provided by several enzymatic antioxidants: superoxide dismutase, catalase and peroxidase glutathione. It has also been suggested that natural antioxidants such as vitamin C, vitamin E and ß-carotene could have a protective effect on lung function [6]. In fact, this is not a new idea. There is evidence of protective action by certain foods and nutrients on lung function parameters such as forced vital capacity (FVC) and forced expiratory volume in 1 second (FEV_1_). Along these lines, daily consumption of fruits and vegetables has been inversely associated, independently of adjustments for total calorie intake and body mass, with chronic obstructive pulmonary disease (COPD) [7,8]. Fibre intake has also shown an inverse relationship with the development of COPD in long-term observational studies [9,10]. Omega-3 fatty acids found in certain fish and seafood may also help to prevent lung disease. A cross-sectional study of the ARIC cohort has demonstrated the protector effect of these dietary elements in smokers and exsmokers with COPD [11]. The relationships between lung function and saturated fats, or polyunsaturated fats, suggest that some of the inflammatory mechanisms of atherosclerosis could be involved in the physiopathology of COPD and some researchers have even suggested the use of cholesterol-lowering medications such as statins in COPD for their anti-inflammatory effect [12].

At present, however, the analysis of dietary patterns is considered the best approach in the study of the health effects of food intake, rather than a focus on specific foods or nutrients, because the diet as a whole incorporates all of the synergistic effects of all foods consumed [13]. In a recent U.S. study with a 3 –year follow-up, the eating habits of 15,567 participants were assessed using a healthy eating index (HEI-2005). The authors describe a significant positive association between lung function and consumption of omega-3 polyunsaturated fatty acids and dietary fibre and a negative association with total intake of calories and saturated fatty acids [14]. The traditional dietary pattern in Mediterranean countries, the Mediterranean Diet (MD), encompasses a combination of characteristic foods such as fruits, vegetables and fresh produce, fish and seafood, nuts, legumes/pulses and olive oil. These foods are rich in antioxidants such as vitamin C, vitamin E, ß-carotene, phytoestrogens, folates or selenium and mono- and polyunsaturated fatty acids, and have a low percentage of saturated fats and cholesterol. This MD pattern has been associated with large reductions in the incidence of major cardiovascular events and in all-cause mortality [15,16].

Although it would obviously be of interest if this dietary pattern could be recommended for purposes other than the prevention of cardiovascular diseases, insufficient empirical evidence is available to establish improved lung function in smokers with better MD adherence [17].

The aim of the study is to evaluate the effects of a nutritional education intervention designed to increase adherence to the MD pattern, compared to the participant’s usual diet, on lung function in smokers with no previous respiratory disease.

## Methods

### Study design

The DIET study (Diet, Spirometry and Tobacco) is a randomized, controlled, parallel clinical trial to be carried out in a subsample of participants in the RESET-DIET project. The main project was designed in two phases. The first phase is the RESET study (FIS-2011, PI11/01962), a randomized, controlled, multicentre clinical trial involving current smokers aged 35 to 70 years with no history of respiratory disease. This study aims to evaluate the effectiveness of a motivational intervention based on spirometry information to promote smoking cessation [18]. Participants who are still smoking at the end of the RESET follow-up will be candidates to participate in the second phase: the DIET study [19] (Figure 1: Flowchart of the study).

**Figure 1 Fig1:**
[figure not shown]
**Flowchart of the study: participant selection, randomization and follow-up.**

### Participants

#### Selection of participating primary care centers

Primary health care centers of Reus city (Tarragona) and surrounding areas.

#### Randomization

Individuals who provide signed consent to participate will be randomized (1:1) to two study groups, intervention and control. The groups will be assigned consecutively in a centralized process carried out by the Research Support Unit of the Institut d’ Investigació en Atenció Primària (IDIAP) Jordi Gol, following a simple random number list computer-generated for this purpose using EPIDAT 3.0.

##### Patient inclusion criteria

Men and women aged 35 to 70 yearsCurrent smokers at the time of inclusion (defined as a cumulative smoking habit >10 pack-years, calculated as years of smoking multiplied by the average daily consumption of 20-cigarette packs)Internet access and ability to use new technologies, or having someone available to provide this assistanceSigned informed consent to participate

##### Patient exclusion criteria

Any evidence in the medical records of a history or diagnosis of any type of respiratory diseaseAny chronic or terminal condition that could affect baseline parameters or make it difficult to complete the tests required during the study periodInability to participate in the follow-up for any reasonDeclined to continue study participation

### Intervention

Candidates for study participation will be informed about the DIET study and offered an opportunity to participate in participant selection and randomization (visit 0). Those who accept the invitation and remain eligible after implementing the inclusion/exclusion criteria will be asked to provide signed informed consent and will then be randomly assigned to the control or intervention group. All of the interventions will be carried out by the DIET project nutritionist.

The intervention group participants will begin a Mediterranean Diet Nutritional Education Program specifically designed to increase adherence to the MD pattern. The program will have three components: 1) Individual intervention – a personalized 1-hour visit (visit 1) to explain the MD pattern and the benefits of following it. The main objective will be to modify the dietary pattern rather than to focus on changes in specific foods or micronutrients. The 14-item MD Adherence Questionnaire will be used to assess the implementation of the intervention, support provided, and fulfilment of project objectives. The questionnaire assigns one point to each item and classifies MD adherence as low, moderate or high on the basis of the final score. Educational and visual materials will also be used, such as the Food Pyramid or food groups adapted to the personal habits and preferences of each participant. 2) During this same initial visit, the participant will be given access to the DIET study’s nutritional blog, which will contain information about the MD and its benefits, cooking habits, modified recipes, and other topics of interest. The DIET Blog information will be updated periodically. 3) Finally, with the goal of increasing MD adherence and motivation to make changes in eating habits, participants will be invited to a 30-minute group session. The sessions will highlight the principal MD components and will complement the nutritional education session with information about healthy cooking techniques and about reading and understanding nutritional labels. In addition, participants will have the opportunity to ask questions about following the dietary pattern and about the advice they have received.

All participants will receive two years of follow-up. They will be invited to schedule an annual follow-up visit (visits 3 and 5, Figure 1), which will be the same as visit 1 for the group to which they were randomly assigned. Additionally, participants in the intervention group will be invited to an annual group session (visits 2 and 4, Figure 1) midway between the follow-up office visits.

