### Control group

In a visit lasting about 30 minutes (visit 1), control group participants will provide the necessary study data and receive written dietary recommendations appropriate to their clinical-metabolic situation (advice to control weight, glycaemia, cholesterol, blood pressure, etc.). These patients will then be directed to their family nurse and/or doctor to complete the study’s medical testing: spirometry, 12-lead electrocardiogram and blood tests.

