### Measures

All participants will be contacted by telephone to schedule the **inclusion visit (visit 1)**, which will include the standardized medical tests and completion of a data collection questionnaire containing the following information:Sociodemographic and family data: age, sex, ethnicity, marital status, number of children, education level, socioeconomic status, employmentHistory of diseases and respiratory symptomsTobacco use: current number of cigarettes/day), cumulative consumption (packs/year) and age when the participant started smokingDietary habits and lifestyleAlcohol use, measured in units/week (one unit = 10 gr alcohol)Food Frequency Questionnaire [20]Questionnaire on MD Adherence (14 points) [21]Minnesota Leisure Time Physical Activity Questionnaire, validated for the population of Spain [22]Basic physical examination, including weight (Kg), height (cm), body mass index (BMI = Kg/m^2^), waist circumference (cm) and blood pressure (mmHg)Exhaled carbon monoxide measured by carboximetry12-lead electrocardiogramBasic blood tests to measure glucose, triglycerides, cholesterol (total, high-density lipoprotein and low-density lipoprotein, creatinine and transaminases (aspartate-aminotransferase and alanine-aminotransferase).Forced spirometry and bronchodilation test to obtain FVC and FEV_1_ values and the FEV_1_/FVC% ratio, following current guidelines [23].

The primary outcome variable to determine whether the objective has been met will be the change in lung function indicated by spirometry, FVC, FEV_1_ and FEV_1_/FVC %. The secondary outcomes variables will be changes in MD pattern, anthropometric measurements (weight, BMI and waist circumference) and smoking habit.

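### The trial's baseline is taken at visit 1, after randomisation and alongside the arm-specific counselling, so the V1 values behind the change analyses are open to influence from the arm

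*Protocol article*

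**What the plan says.** **Allocation.** The Intervention section places selection and randomisation at visit 0. Candidates who accept and remain eligible "will be asked to provide signed informed consent and will then be randomly assigned to the control or intervention group". The Randomization section makes allocation central.

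**Baseline.** Under Measures, participants are telephoned to arrange visit 1, "which will include the standardized medical tests and completion of a data collection questionnaire". The list covers tobacco use, the food frequency questionnaire, the 14-item adherence score, anthropometry, exhaled carbon monoxide and spirometry. Statistical analysis names V1 as the starting point for the dietary comparison with V5. For lung function it says only that the main outcome is measured when the study begins, without placing this before or after allocation.

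**Counselling at the same visit.** For the intervention arm, visit 1 is "a personalized 1-hour visit (visit 1) to explain the MD pattern and the benefits of following it", with access to the blog. For controls it is a visit of about 30 minutes in which data are given and written dietary advice is received. "These patients will then be directed to their family nurse and/or doctor" for spirometry, electrocardiogram and blood tests. On staffing, the Intervention section says: "All of the interventions will be carried out by the DIET project nutritionist".

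**Earlier data.** The Discussion admits only participants who completed RESET and already have the spirometric and nutritional data required.

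**The concern.** Randomisation makes the arms comparable up to the moment of allocation. A baseline measured after that moment keeps this protection only if neither the participant's answers and effort nor the staff's recording can respond to the arm. Here the baseline shares a visit with the first dose of the intervention.

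The self-reported diet scores are the most exposed. A participant may answer the 14-item questionnaire during or after an hour spent explaining the pattern that it scores. The bias could go either way: over-reporting at V1 would hide a later gain, and strict scoring at V1 would inflate it. Spirometry depends on effort, so it is not immune, but the mechanism is weaker.

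There is also a gap in the intention-to-treat analysis. Someone randomised at visit 0 who never attends visit 1 has no V1 value from which to compute a change.

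Adjusting for the V1 value would not cure this, because that value is itself observed after allocation.

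**Working it through.** **1. The order of events, from the text**

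| Step | Intervention arm | Control arm |
|---|---|---|
| Visit 0 | Consent, then allocation | Consent, then allocation |
| Telephone contact | Visit 1 arranged | Visit 1 arranged |
| Visit 1, questionnaires | Same visit as the 1-hour session; order not fixed | Same visit as the written advice |
| Visit 1, spirometry | Operator and order not stated | After the advice, with family nurse or doctor |

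The V1 baseline follows allocation in both arms. In the control arm, the text also places spirometry after advice.

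**2. Which shifts matter**

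Let s1 be the between-arm distortion at V1 and s5 the distortion at V5. The bias in the difference in change (V5 minus V1) is s5 - s1. The Intervention section makes the annual visits (3 and 5) the same as visit 1 within each arm, so a stable arm difference in route or order gives s5 = s1 and cancels. What remains is b, the part of the shift specific to V1.

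**3. The plan's own figure**

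The sample size section gives 40 per group, 10-12 ml/year in FEV1, two-sided 5%, 80% power and under 15% losses. It gives no standard deviation, so 40 cannot be reproduced. The implied value can be solved for with 40 x 0.85 = 34 evaluable per group:

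- SD = d x sqrt(n/2) / (1.960 + 0.842)
- d = 10: 10 x sqrt(17) / 2.802 = 14.7 ml/year
- d = 12: 12 x sqrt(17) / 2.802 = 17.7 ml/year

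**4. Scale of a V1-specific shift (illustration only)**

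The two-year target is 2 x 10 to 2 x 12 = 20-24 ml. The documents give no value for b, so 5, 10 and 20 ml are assumptions. A shift b at V1 changes the annual rate over two years by b/2. If the trial has its stated 80% power, the standard error is d/2.802, so the standardised bias is 2.802 x b/(2d). With no true effect, the two-sided error rate is 1 - Phi(1.960 - bias) + Phi(-1.960 - bias).

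| Assumed b | Share of target (b/24 to b/20) | Bias in SE units (d = 12 to d = 10) | False-positive rate |
|---|---|---|---|
| 5 ml | 21-25% | 0.58-0.70 | 9-11% |
| 10 ml | 42-50% | 1.17-1.40 | 22-29% |
| 20 ml | 83-100% | 2.34-2.80 | 65-80% |

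If the true standard deviation exceeds 14.7-17.7 ml/year, the standard error is larger and these rates are lower, but the bias in ml is unchanged.

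**The case against.** The strongest objection is that the title outcome is better protected than the visit order suggests. Several parts of it stand.

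- **Earlier measurements exist.** A reader might infer that randomisation precedes any measurement. The Discussion rules this out: spirometric and nutritional data from RESET are a condition of entry. However, nothing in the article makes them the DIET baseline, and the dietary baseline is explicitly V1.
- **Who performs spirometry.** A reader might infer that the unmasked nutritionist takes the primary-outcome baseline. The text does not say so. Controls are sent to their nurse or doctor, and no operator is named for the other arm. The nutritionist's role in collecting the dietary data is implied in the Discussion, and that is where exposure is clearest. Change in diet pattern is a secondary outcome.
- **Not every change score is affected to the same degree.** Stable arm differences recur at V5 and cancel, and the documents show no mechanism by which a diet session alters FEV1 at V1 only.
- **Selection at entry is not the issue.** Central allocation protects concealment, and the plan will check whether losses depend on arm.
- **This is a condensed article.** Operators and order within a visit may be fixed in the full protocol, and the flowchart is not shown. That excuses the silence on the intervention arm. It does not remove the two orders that the article does state: allocation before V1, and control spirometry after advice.

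**Conclusion.** The point stands in this limited form. The article fixes allocation at visit 0 and the DIET baseline at a later visit that also delivers arm-specific advice, so V1 values lack the protection of a pre-allocation measurement. The self-reported diet scores are the most exposed; spirometry is exposed to a lesser and less certain extent. Participants lost between visits 0 and 1 have no V1 value for the intention-to-treat change analysis, and no pre-randomisation value is designated in its place.

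The size of any bias is unknown, and the documents do not show that a shift will occur. The illustration rests on assumed shifts, on those shifts being specific to V1, and on the trial having its stated power. It shows only that a target of 20-24 ml leaves little room: a shift of 5 ml would be about a fifth to a quarter of the effect sought. The change is worth making because prevention is cheap and analysis of V1 data cannot undo the problem afterwards.

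**What to change.** Re-order the existing steps. After consent, complete the V1 questionnaires and spirometry in both arms. Only then should the central unit release the allocation, followed by the arm-specific session or written advice. State in the plan that no dietary advice precedes these measurements.

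Where this is not feasible, prespecify the pre-randomisation RESET end-of-study values as the baseline. Before relying on them, confirm that they include the same spirometric measures and dietary instruments and state how old they are at DIET entry; the article gives neither.

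**Cost.** The tests are unchanged and central allocation already exists. Counselling would start after a short delay and, because control testing runs through the family nurse or doctor, some participants may need a second appointment. The change does not require the same operators in both arms or a different randomisation list.

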### Control group

In a visit lasting about 30 minutes (visit 1), control group participants will provide the necessary study data and receive written dietary recommendations appropriate to their clinical-metabolic situation (advice to control weight, glycaemia, cholesterol, blood pressure, etc.). These patients will then be directed to their family nurse and/or doctor to complete the study’s medical testing: spirometry, 12-lead electrocardiogram and blood tests.

### Measures

All participants will be contacted by telephone to schedule the **inclusion visit (visit 1)**, which will include the standardized medical tests and completion of a data collection questionnaire containing the following information:Sociodemographic and family data: age, sex, ethnicity, marital status, number of children, education level, socioeconomic status, employmentHistory of diseases and respiratory symptomsTobacco use: current number of cigarettes/day), cumulative consumption (packs/year) and age when the participant started smokingDietary habits and lifestyleAlcohol use, measured in units/week (one unit = 10 gr alcohol)Food Frequency Questionnaire [20]Questionnaire on MD Adherence (14 points) [21]Minnesota Leisure Time Physical Activity Questionnaire, validated for the population of Spain [22]Basic physical examination, including weight (Kg), height (cm), body mass index (BMI = Kg/m^2^), waist circumference (cm) and blood pressure (mmHg)Exhaled carbon monoxide measured by carboximetry12-lead electrocardiogramBasic blood tests to measure glucose, triglycerides, cholesterol (total, high-density lipoprotein and low-density lipoprotein, creatinine and transaminases (aspartate-aminotransferase and alanine-aminotransferase).Forced spirometry and bronchodilation test to obtain FVC and FEV_1_ values and the FEV_1_/FVC% ratio, following current guidelines [23].

The primary outcome variable to determine whether the objective has been met will be the change in lung function indicated by spirometry, FVC, FEV_1_ and FEV_1_/FVC %. The secondary outcomes variables will be changes in MD pattern, anthropometric measurements (weight, BMI and waist circumference) and smoking habit.

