### Sample size/power calculation

A sample of 40 participants in each group will be required to observe significant differences in lung function between groups (decrease in FEV_1_ > 10–12 ml/year), in a two-tailed test with a mean FEV_1_ value of 95%, significance level of 5%, 80% strength and less than 15% losses to follow-up [24].

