### Statistical analysis

The study will use an intention-to-treat analysis and the main outcome variable will be measured at the beginning of the study for each participant. The effectiveness of the simple randomization will be evaluated by the comparability and homogeneity of the two groups in terms of the baseline distribution of the study variables. Losses to follow-up will be calculated for each group and evaluated to determine whether the proportion of losses is independent of assignment to the intervention or control group.

Qualitative variables will be described as frequencies or percentages and quantitative variables by means and standard deviations if they follow a normal distribution, or median and interquartile range.

Variables will be stratified by study group; basal comparison will be done by x^2^ test for qualitative variables and Student t or Mann–Whitney U for quantitative variables. Data from the initial MD Adherence Questionnaire and Food Frequency Questionnaire (V1) will be compared to the final questionnaire data (V5). In addition, changes from baseline in lung function after the corresponding nutritional intervention, will be compared for both groups. If important clinical differences are observed, multivariate analysis will be used to determine which factors are independently associated with the outcomes, adjusting for covariates such as age, sex, ethnic group, height, BMI, education level, smoking habit, physical activity or total caloric intake [6]. The results will be presented using relative measures including relative risk (RR) and relative risk reduction (RRR), and absolute risk reduction (ARR), with 95% confidence intervals. All analysis will be done with SPSS version 22.0, considering differences to be significant when *p* < 0.05.

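### Three spirometry measures jointly decide success at an unadjusted 0.05 while the trial is sized on FEV1 alone, so the stated 5% error and 80% power do not describe the trial's decision

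*Protocol article*

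**What the plan says.** Measures gives the primary outcome a deciding role: "The primary outcome variable to determine whether the objective has been met". The sentence goes on to say that this variable "will be the change in lung function indicated by spirometry, FVC, FEV_1_ and FEV_1_/FVC" %. The abstract does the same: "Primary outcome is lung function indicated by spirometry, FVC, FEV1 and FEV1/FVC" %. Neither place ranks the three.

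Statistical analysis states the comparison as "changes from baseline in lung function after the corresponding nutritional intervention, will be compared for both groups", and sets one threshold for all analyses: "considering differences to be significant when *p* < 0.05". The same section refers to the main outcome variable in the singular, although Measures names three.

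Sample size/power calculation opens with "A sample of 40 participants in each group will be required to observe significant differences in lung function between groups". The only effect it then gives is an FEV1 difference of more than 10–12 ml/year, "in a two-tailed test with a mean FEV_1_ value of 95" %, at 5% significance, 80% power and under 15% losses. It gives no effect for FVC or for the ratio. Nowhere is FEV1 declared the single primary measure.

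**The concern.** A primary outcome that decides success has to lead to one decision. Here three measures, one of them computed from the other two, share that role, and no statement turns three p-values into one verdict. The 5% and 80% in the sample size section belong to a single test of FEV1. They carry over to the trial's conclusion only if FEV1 alone decides, and the document does not say that it does.

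Two things are at stake. One is the error rate, if any favourable p-value may be reported as meeting the objective. The other is the meaning of the result, if the three measures point in different directions. The Discussion concedes that the study period may be too short to show clear differences. When a true effect is expected to be hard to detect, a free choice among three p-values is especially likely to mislead.

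**Working it through.** **Inputs from the document.** Three primary measures (Measures; abstract). Threshold 0.05 for all analyses (Statistical analysis). Two-sided test, 5%, 80%, losses under 15%, 40 per group, FEV1 difference 10–12 ml/year (Sample size/power calculation). Allocation 1:1 (Randomization). **Not in the document:** any standard deviation (SD) of FEV1 change, and any correlation between the three changes. The correlations below are assumptions.

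**1. The plan's own figure.** Without an SD, 40 per group cannot be recomputed. It can only be solved backwards. With 15% losses, 40 × 0.85 = 34 per group are evaluable. From n = 2(1.960 + 0.842)² SD²/d², n = 34 gives SD = 14.7 ml/year for d = 10 and 17.7 ml/year for d = 12. This is one test of one measure; FVC and the ratio do not enter it.

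**2. If any one significant measure counts as success.**
- Independent tests: 1 − 0.95³ = 14.3%. For two-sided tests on jointly normal statistics, this is the largest possible value.
- Independence cannot hold here. On the log scale, ratio = FEV1 − FVC. Let r be the correlation of the FEV1 and FVC changes, and k the ratio of their SDs (FEV1 over FVC). Then corr(FEV1, ratio) = (k − r)/√(k² + 1 − 2rk) and corr(FVC, ratio) = (rk − 1)/√(k² + 1 − 2rk). Both are zero only if k = r and rk = 1, that is r² = 1, where FEV1 and FVC are themselves perfectly correlated.
- Simulated chance of at least one p < 0.05 when there is no effect (1,000,000 draws per cell):

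| r | k = 0.8 | k = 1 | k = 1.25 | k = 1.5 |
|---|---|---|---|---|
| 0.5 | 12.1% | 12.2% | 12.1% | 11.8% |
| 0.8 | 11.5% | 11.8% | 11.4% | 10.8% |
| 0.9 | 10.7% | 11.3% | 10.6% | 9.8% |
| 0.95 | 9.8% | 10.9% | 9.8% | 8.7% |

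The range is 8.7–12.2%, or about 9–12%, roughly twice the nominal 5%.

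**3. If all three must be significant.** A joint event is no more likely than any of its parts. The false-positive rate is therefore at most 5%. By the same argument power is at most that of the FEV1 test, so the planned 80% becomes an upper limit.

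**4. If FEV1 alone decides.** The error is 5%, and the planned power refers to the right test. This is the only one of the three rules that matches the sample size section.

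**5. Conflict between measures.** With illustrative values, FEV1 goes from 3.00 to 3.10 L (+3.3%) and FVC from 4.00 to 4.30 L (+7.5%). The ratio goes from 3.00/4.00 = 75.0% to 3.10/4.30 = 72.1%. Two measures improve and the third worsens, and the document does not say what the verdict would be.

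**The case against.** The strongest reply is that this is a condensed article, and testing order and multiplicity are often left to an analysis plan that is not shown. That stands as far as it goes: the absence of an adjustment is not in itself a finding. But the choice of primary outcome and the significance threshold are settled at protocol level, and the article states both. What it states does not fit its own sample size section.

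A second reply is that sizing on FEV1 shows that FEV1 was meant to lead. That is plausible and makes the repair easy, but the text never says so, and Measures and the abstract say something else.

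A third is that the threshold applies to all analyses and the document does not describe three separate primary tests. That is true. Reading it as three tests at 0.05 is a reasonable inference, not a stated plan.

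A reader might go further and infer that the trial's false-positive rate is 14%, or that it is certainly inflated. The document supports neither. The 14% needs independence, which a ratio derived from the other two measures rules out. Any inflation requires the any-one rule, which is not written down; if all three were required there would be none.

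Finally, this is a small pragmatic trial that presents its results as additional evidence. That limits the consequences but does not remove the ambiguity.

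**Conclusion.** The point holds. Three measures are given the role of deciding whether the objective is met, under one unadjusted threshold, while the design figures refer to FEV1 alone. Under the any-one rule the false-positive rate is about 9–12% instead of 5%. This assumes FEV1–FVC correlations of 0.5–0.95, SD ratios of 0.8–1.5 and a ratio that follows from the other two. Under the all-three rule the error is at most 5% and the 80% power is only an upper limit. Under either rule, the stated error and power are not both those of the trial's decision. The size of the inflation depends on assumed correlations and an assumed success rule. The mismatch between the primary outcome and the sample size does not.

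**What to change.** In the abstract and in Measures, name change in FEV1 from baseline, in the ml/year form used in the sample size section, as the single primary outcome, tested two-sided at 5%. List FVC and FEV1/FVC % as secondary, reported with 95% confidence intervals and no confirmatory claim. Add a clause on how the yearly change is derived from the annual spirometries: Statistical analysis ties visits 1 and 5 to the questionnaires, not to spirometry. Make the change before outcome data are compared between groups, since a choice made afterwards would not be credible.

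The cost is a short edit in each of these places. The registry entry was not available, so whether it also needs changing has to be checked. The number of participants stays at 40 per group. The price is that FVC and the ratio can no longer establish success on their own.

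If all three must keep a confirmatory role with any one sufficing, a Bonferroni split tests each at 0.05/3 = 0.0167. A comparison planned for 80% power would then have about 66%, or need about 1.33 times the sample (40 × 1.334 = 53.4, so 54 per group). Naming one primary measure is cheaper and fits the existing calculation.
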